### Participants and Recruitment

Students aged 17 to 35 years from the UON, Australia, were recruited for the pilot study. Exclusion criteria included having a medical condition requiring a prescribed diet (eg, diabetes). The participants were recruited via posts on the University social media pages (Facebook and Twitter) and posters and digital signage displayed across University campuses. The recruitment was also supported by the project steering committee that further promoted the study via personal networks within the university. Participants were reimbursed for their time, including a gift voucher to the value of Aus $10 after completing baseline measures and a second gift voucher to the value of Aus $10 after completing follow-up measures. All measures, including baseline, follow-up, and process evaluation, were collected via Web-based surveys conducted using Qualtrics Survey Platform (Qualtrics).

#### Sample Size

As this is a pilot study, a formal sample size calculation was not performed. The total sample size was set at 126 (ie, 63 per group). This would exceed the median sample size of 30.5 among nondrug trials in a review of the methods and conduct of pilot and feasibility trials [49], ideally allowing for more diversity within the sample in terms of sociodemographics and student-related characteristics, and this was also based on the time available for recruitment to allow the study to be conducted within the university semester (5 weeks), as well as study funding. As males are often underrepresented in health behavior research, a lower limit of 30% of the target sample size being male was set, which would exceed the proportion of males typically achieved in previous intervention studies among this target group [7]. To maximize the number of male participants enrolled, interested females were waitlisted once the proportion of females reached 70% of the target sample size. As the proportion of 30% male participants was unable to be reached, female participants were invited from the waitlist until the recruitment period was complete.

#### Randomization

Randomization was conducted by an external statistician. Allocation was stratified by gender (female; male and other gender identity). Allocation sequences within strata were generated by a statistical software program, using permuted block randomization with random block sizes of 2 and 4.

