#### Phase 2: Epidemiological, Behavioral, and Environmental Assessment

Phase 2 was focused on developing a logic model of the health problem, linking the health problem to environmental and behavioral determinants [22]. During this phase, the goal was to identify the priority eating behaviors and determinants to be targeted and addressed in the intervention. To achieve this, the literature was reviewed and a cross-sectional analysis of the data from the UON Student Healthy Lifestyle Survey (SHLS) 2016 was conducted. From the literature, it was identified that students typically have low consumption of nutrient-rich foods, particularly fruits and vegetables [27], and high consumption of energy-dense, nutrient-poor foods, especially takeaway foods and confectionary [28,29]. In addition, the major determinants influencing eating behaviors were found to be environmental factors such as living situation, social environment, financial status, as well as personal factors such as age and gender [30-34]. Gaps in the evidence base included that there are few studies among university students that explore a broad range of eating behaviors and the associations among them, as well as a broad range of determinants. Furthermore, there is a distinct lack of studies of this nature in Australian students. The cross-sectional analysis of the SHLS included 4383 students (70.59% [3094/4383] female; mean age 25.5 (SD 9.3) years, and 92.01% [4033/4383] domestic students). Eating behaviors were assessed using short diet questions relating to consumption of fruits, vegetables, breads, cereals, red meat, a range of discretionary (ie, energy-dense and nutrient-poor) food categories (eg, confectionary, processed meat products, and hot chips, wedges or fried potatoes), and breakfast [35]. The priority eating behaviors identified were fruits (45.74% [2005/4383] consuming <2 servings per day), vegetables (91.31% [4002/4383] consuming <5 servings per day), discretionary foods (eg, 68.67% [3010/4383] consuming confectionary 1-2 times per week or more; 54.55% [2391/4383] consuming hot chips, wedges or fried potatoes 1-2 times per week or more), and breakfast (41.75% [1830/4383] not consuming daily). The key determinants identified were living situation, gender, and faculty of study, with females, students living in their own home or on-campus, and students enrolled in the Faculty of Health and Medicine found to have healthier eating behaviors overall [36].

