### Data Analysis Plan

Data will be analyzed using Stata software version 14.1 (StataCorp LLC). Process evaluation data will be reported as means and SDs for quantitative questions, for example, scoring of individual program components such as usefulness of the goal-setting feature, and open question responses, such as suggested improvements for EATS, will be compiled and described qualitatively. Intervention usage will be assessed via analysis of usage metrics, including the time spent completing individual components and number of times the links were accessed, to allow comparison with other electronic health (eHealth) research studies. Impact evaluation, that is, to determine the efficacy of the EATS program compared with the control, will be determined using an intention-to-treat approach. All the results for all the participants who enter the study will be included in the analyses. Analyses will assess the difference between the intervention and control groups for the change from baseline to 3 months for all outcomes. Each study effect will be tested as the group by time interaction using a linear mixed model where time will be treated as a repeated measure. The effect sizes and 95% CIs will be reported for each outcome measure. A sensitivity analysis will be conducted to explore the impact of missing data on the primary impact evaluation measure (diet quality).

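### Allocation is stratified by gender, but the mixed model as described does not include the stratum; the effect is small and two model terms would fix it

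*Protocol article*

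**What the plan says.** The Randomization section of the protocol article states: "Allocation was stratified by gender (female; male and other gender identity"). Sequences within strata were generated "using permuted block randomization with random block sizes of 2 and 4". In Phase 2 the team's own survey of 4383 students gives a reason to expect gender to matter: "The key determinants identified were living situation, gender, and faculty of study".

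The Data Analysis Plan gives one model for all impact outcomes: "Each study effect will be tested as the group by time interaction using a linear mixed model". The target is the "difference between the intervention and control groups for the change from baseline to 3 months for all outcomes". On the analysis set it says "All the results for all the participants who enter the study will be included in the analyses", and on reporting "The effect sizes and 95% CIs will be reported for each outcome measure". A sensitivity analysis for missing data is planned for diet quality. No covariate is named in the model or in that sensitivity analysis, and the text does not say that the model is unadjusted.

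**The concern.** Stratified allocation removes chance imbalance in gender between the arms. An analysis gets the benefit only if the stratum is in the model. Otherwise the variation in change between genders stays in the residual variance, and the reported interval is wider than the design warrants.

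The second issue is missing follow-up. A likelihood-based mixed model relies on data being missing at random given what the model contains. If dropout depends on gender and arm together, that condition holds only with gender included.

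At stake are a little precision on every impact outcome and some protection against one particular dropout pattern. The article also reports that follow-up is complete and analysis is under way, so its text does not show that a gender adjustment was settled before the outcome data were available.

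**Working it through.** **Inputs.** From the article: 126 participants, 63 per group (2 × 63 = 126; no power calculation to reproduce); two gender strata; blocks of 2 and 4; two visits. The Sample Size section says that the 30% male floor (0.30 × 126 = 37.8) was not reached, but gives no final share. Assumed, because the article gives no values: a male/other share *p* of 20–30%, a gender difference in change *g* (in units of the within-gender SD of change), visit correlation 0.6, a gender gap in level of 0.4 SD, and all dropout rates.

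**Step 1: which term matters.** With complete data at two visits, the group-by-time estimate equals the difference between arms in mean change. A gender difference in level cancels within each person's change, so a stratum main effect alone leaves the estimate as it was. Only stratum-by-time can alter it.

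**Step 2: interval width.** Without gender, the model's variance of change is σ²(1 + p(1 − p)g²). Under stratified allocation the contrast varies according to σ² alone. The width ratio, gender omitted to gender-by-time included, is therefore k = √(1 + p(1 − p)g²), and actual coverage is 2Φ(1.96k) − 1. For example, p = 0.25 and g = 0.5 give √(1 + 0.1875 × 0.25) = 1.0232.

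| g | p = 0.20 | p = 0.25 | p = 0.30 | Coverage |
|---|---|---|---|---|
| 0.2 | 1.0032 | 1.0037 | 1.0042 | 95.1% |
| 0.3 | 1.0072 | 1.0084 | 1.0094 | 95.2% |
| 0.5 | 1.0198 | 1.0232 | 1.0259 | 95.4–95.6% |
| 0.8 | 1.0500 | 1.0583 | 1.0651 | 96.0–96.3% |

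All errors are on the conservative side.

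**Step 3: dropout.** Simulation with 5000 runs per scenario, 126 participants, 25 or 38 of them in the male/other stratum, the stated strata and blocks, g = 0, 0.3 or 0.5, and the same treatment effect in both strata:

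- Dropout 40% in men and 20% in women, equal in both arms: bias at most 0.006 SD of change, with or without gender, which is within simulation error.
- Dropout in men 50% (intervention) against 20% (control), with women 20% in both arms or 20% against 30%: absolute bias 0.007–0.035 SD without gender and at most 0.003 SD with gender and gender-by-time. Mean interval width without gender was 0.79–0.83 SD, a half-width of about 0.4. Coverage was 94–96% either way.

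**Step 4: hand check of the largest bias.** With 38 men and 88 women there are about 19 and 44 per arm. Expected completers are 9.5 and 35.2 in the intervention arm (male share 0.2125) and 15.2 and 30.8 in the control arm (0.3304), a difference of −0.118. The SD of change is √(2 × 0.4) = 0.894. Given baseline, the remaining gender gap at follow-up is about −0.4 × (1 − 0.6) + 0.5 × 0.894 = 0.287. The bias is then −0.118 × 0.287 / 0.894 = −0.038 SD, close to the simulated −0.035.

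Here men start lower and change more. If they started lower and also changed less, the gap would be −0.16 − 0.447 = −0.607 and the bias −0.118 × −0.607 / 0.894 = 0.080 SD, about a fifth of the half-width. So 0.035 is the largest value in the simulated scenarios, not an upper bound.

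**The case against.** The strongest objection is that the article is silent rather than explicit. It names the tested term, does not list all fixed effects, and nowhere says that gender is left out. Covariate lists are commonly left to the full protocol or SAP, which are not shown. This stands: a reader might infer that the stratification is deliberately ignored, but the text shows only that the model as described does not include it. If a fuller plan lists the stratum, the point falls away.

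A reader might also infer that the intervals are too narrow or invalid. The calculation shows the opposite direction and a small size. The survey finding concerns level of eating behavior, not change over three months, so nothing in the article supports a large *g*; at g = 0 the simulated widths with complete data were the same with and without gender.

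A third tempting reading is that gender-related dropout in general goes unhandled. It does not follow: dropout by gender that is equal across arms produced no bias, the planned mixed model can retain participants seen only at baseline, and a missing-data sensitivity analysis is planned for diet quality. What remains is that no such analysis is stated for the other impact outcomes, and that the described model cannot absorb dropout depending on gender and arm jointly.

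Finally, this is a feasibility pilot without a formal sample size calculation, so a gain of a percent or two in interval width is of little practical weight. That is fair and sets the priority.

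**Conclusion.** The point holds as a low-priority improvement. The stratifier shapes allocation but is absent from the described model. Omitting it makes the intervals conservative by about 0–3% for a gender difference in change of up to 0.5 SD, with coverage of 95.0–95.6%. It leaves a small bias, up to about 0.035 SD in the simulated scenarios, only where dropout differs by both gender and arm. No inflated false-positive rate is shown.

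These sizes rest on the assumed male/other share, visit correlation, gender gaps and dropout rates, and on a treatment effect common to both strata. If the effect itself differed by gender, stratum and stratum-by-time would not resolve it, because that needs a three-way term.

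**What to change.** Add the randomization stratum (female versus male/other) and stratum-by-time as fixed effects to the planned linear mixed model for every impact outcome, and carry both into the missing-data sensitivity analysis for diet quality. Including only the main effect would not be enough, for the reason in step 1. The mixed model itself need not be replaced. If the full plan already contains these terms, a sentence saying so is sufficient.

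The cost is two model terms, using a variable that was needed to randomize and is therefore held for every participant.

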#### Control Group

Attention control group participants completed Thrive, a brief Web-based intervention designed for university students with a focus on alcohol intake [50]. Thrive provides feedback on their current alcohol intake and related risk, as well as links to further resources for support. The control group participants also received access to the EATS intervention after completing follow-up measures.

### Measures

#### Process Evaluation Measures

##### Program Acceptability

Program acceptability, including satisfaction, usability, and appropriateness, was evaluated using a process evaluation survey developed for the study. Participants were asked to rate each of the components (quiz, goal setting, and creating strategies) as well as the website overall on a 5-point Likert scale from strongly agree (5) to strongly disagree (1) for usefulness, relevance, usability, and ability to motivate. Participants also rated their overall satisfaction with the EATS intervention, from very satisfied (5) to very unsatisfied (1); whether the intervention met their expectations, from strongly agree (5) to strongly disagree (1); and their opinion on the length of the intervention, from too much time (5) to too little time (1). The participants were also asked a series of open-ended questions relating to their likes and dislikes and suggestions for improvement for each of the intervention components and the intervention overall, as well as reasons for not visiting Web pages or using intervention components where relevant.

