## Discussion

### Principal Findings

This project used the PRECEDE-PROCEED model to develop a brief Web-based nutrition intervention for young adult university students and plan the evaluation. Nutrition interventions are needed in this target group because of the high rates of unhealthy eating behaviors and the known impacts of this on health and well-being and long-term chronic disease risk [56]. The difficulty is in engaging young adults because of the transitional nature of this life stage and the many factors influencing their health behaviors [9].

The pilot RCT will evaluate whether EATS is deemed acceptable and appropriate by young adult university students and whether it can improve diet quality over a 3-month follow-up period. The process evaluation will provide important feedback from the target population on the appropriateness of the mode of delivery, intervention duration, and individual intervention components. This will be utilized to update and modify the intervention, whereas the intervention usage data will be compared with other eHealth studies to assess participant engagement. Utilizing the university setting, as well as the eHealth mode of intervention delivery, shows promise as a means of effectively targeting and engaging young adults [14,57]. In addition, the development of EATS as a brief intervention draws on the precedence of successful brief interventions to reduce alcohol use among university students [20]. Therefore, the combination of a strong methodological approach to intervention development, the use of a setting with the potential for wide reach among young adults, and the use of an intervention approach with demonstrated efficacy suggest that the EATS intervention may be successful.

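### The two-ended item on intervention length is to be summarized by mean and SD, which cannot show what share found EATS too long, too short or about right (minor)

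*Protocol article*

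**What the plan says.** **The item.** Protocol article, Program Acceptability: participants give "their opinion on the length of the intervention, from too much time (5) to too little time (1". Only the two ends carry labels.

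**The other closed items.** The same section has ratings of usefulness, relevance, usability and motivation, a rating of whether expectations were met, and "overall satisfaction with the EATS intervention, from very satisfied (5) to very unsatisfied (1". All of these run from unfavourable (1) to favourable (5).

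**The summary rule.** Data Analysis Plan: "Process evaluation data will be reported as means and SDs for quantitative questions". The example given there is the usefulness of the goal-setting feature, a one-directional item. No exception is stated for the length item, and no category counts are mentioned.

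**The use of the result.** Principal Findings: the process evaluation is to give feedback on the "appropriateness of the mode of delivery, intervention duration, and individual intervention components", and this feedback will be used to update the intervention.

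**Other information on length.** Participants are asked "a series of open-ended questions relating to their likes and dislikes and suggestions for improvement", and the answers will be described qualitatively. Website visit duration is tracked (Intervention Usage), and time spent on individual components is to be analysed (Data Analysis Plan).

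**The concern.** A mean suits a rating on which more is better. On the length item the favourable answer lies in the middle, so a mean near 3 can come from general contentment or from two opposite groups of complaints. These call for different actions: none if most people find the length right, and a choice between shortening, lengthening or offering options if opinion is divided.

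The question is not incidental. The article gives lack of time as a main barrier for this population, and EATS was built as a single-use programme of about 25 minutes for that reason. This is the only closed item described that asks participants what they thought of the length.

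**Working it through.** The article gives no figure for this item, so there is nothing to reproduce. The check is whether mean and SD together determine the shares that matter.

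**Inputs**
- Scale 1 to 5, both ends unfavourable (Program Acceptability).
- Planned summary: mean and SD (Data Analysis Plan).
- Number of raters: assumed to be about the size of the EATS group. Sample Size: "The total sample size was set at 126 (ie, 63 per group". The number who answered is not given. I use 64 because it is close to 63 and divides evenly.
- Assumption: 3 means about right.

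**Formula.** When the mean is 3, SD = √[Σ(x − 3)² / (n − 1)].

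**Step 1: the extreme contrast**
- All 63 raters at 3: mean 3.00, SD 0.
- 31 at 1 and 31 at 5 (n = 62): mean 3.00; Σ = 62 × 4 = 248; SD = √(248/61) = 2.02.

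The means agree, but the SD separates the two.

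**Step 2: less extreme patterns, n = 64**

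| Pattern | Σ(x − 3)² | Mean | SD | Too little (1–2) | Midpoint (3) | Too much (4–5) |
|---|---|---|---|---|---|---|
| 8 at 1, 48 at 3, 8 at 5 | 16 × 4 = 64 | 3.00 | √(64/63) = 1.01 | 12.5% | 75% | 12.5% |
| 32 at 2, 32 at 4 | 64 × 1 = 64 | 3.00 | √(64/63) = 1.01 | 50% | 0% | 50% |

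The whole planned summary is identical, while the midpoint share is 75% in one row and 0% in the other.

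**Step 3: how wide the ambiguity is.** At mean 3, each answer off the midpoint adds either 1 or 4 to Σ. With k such answers, k ≤ Σ ≤ 4k. For Σ = 64 this gives 16 ≤ k ≤ 64, so the midpoint share can lie anywhere from 48/64 = 75% down to 0%. The two rows above are the limits of that range.

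**Step 4: the planned group size of 63.** With 8 at 1, 47 at 3 and 8 at 5, the mean is 3.00, the SD is 1.02 and 74.6% are at the midpoint. With 31 at 2, 1 at 3 and 31 at 4, the mean is 3.00, the SD is 1.00 and 1.6% are at the midpoint. The choice of 64 does not drive the result.

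**The case against.** **The SD is part of the plan.** This stands in part. A reader might infer that the planned summary can never tell an ideal result from a divided one. The documents do not support that, because an SD is to be reported and it exposes the extreme split (0 against 2.02). A small SD is also informative. At mean 3 the share off the midpoint cannot exceed Σ/n, which is at most SD², so an SD of 0.5 guarantees at least 75% at the midpoint. A one-sided complaint would show in the mean. The ambiguity is confined to larger SDs, but an SD near 1 is enough to produce it.

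**Points 2 to 4 are unlabelled in the article.** This stands as a limit. A reader might count every answer off the midpoint as dissatisfaction. If answers were spread 10/20/40/20/10% over 1 to 5, that count would be 60%, but only 20% would have chosen a labelled complaint. The article does not say which count is right.

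**The article is a condensation, and per-category counts could be in the full document.** If they are, nothing needs to change. But the article does state a summary rule for these questions, and that rule, applied as written, is the wrong one for this item.

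**Other data bear on length.** They do, but only in part. Open-ended answers may mention length without giving shares, and tracked times measure time spent, not opinion of it.

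**The item might be averaged into an overall acceptability score.** A reader might fear this, but no section proposes a composite, so it is no part of the point.

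**Conclusion.** The point holds and is minor. Applied as written, the rule gives a summary of the length item that can be the same (mean 3.00, SD 1.01) whether 75% or 0% of raters are at the midpoint. It therefore cannot report the shares finding EATS too long, too short or about right, although feedback on duration is meant to guide revision of the programme. This rests on two assumptions: that 3 means about right, and that the stated rule covers the length item, as nothing exempts it.

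It would go too far to infer that the acceptability evaluation as a whole is unsound. Means and SDs follow the direction of the other closed ratings. The length item feeds no stated test, sample size or threshold, and the diet-quality analysis is untouched.

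**What to change.** For the length item, report the number and percentage of respondents in each of the five categories, and the midpoint percentage with its 95% CI. This can replace the mean and SD or stand beside them. Print the wording of all five response options with the table, so that the meaning of the midpoint does not have to be assumed. The other ratings can stay as planned.

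The cost is one table row in a different format. The article's Results section says that follow-up data collection is complete and analysis is under way, so no new data are needed.
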